**(2) Schedule**

| List | Screening | Follow-up | Close |
| --- | --- | --- | --- |
| Check inclusion/exclusion criteria | X |  |  |
| Demography | X |  |  |
| Diagnosis, pathological results, complications | X | X |  |
| Body component |  | X |  |
| QoL questionnaire |  | X |  |
| Nutritional parameters |  | X |  |
| Use of smartphone app. |  | X |  |
| Report |  |  | X |

(3) **Study period**

- Research participation period: One year after gastrectomy for early gastric cancer

- Data collection period: IRB approval day – 2021. 12. 31

- Overall study period: IRB approval day – 2022. 6. 30.

**9. Statistical Methods**

(1) **Randomization**

- Randomization generally performs permutated mixed block randomization, and is generated in a 1:1 ratio using 2 and 4 mixed block blocks. Using the nQuery Program, a randomly assigned table is created according to the stratification factor and notified through a web-based clinical research management system.

- Stratification factors: extent of gastrectomy (distal vs. total gastrectomy)

(2) **Statistical analyses**

- Patient's clinical characteristics are expressed as mean ± standard deviation or ratio using descriptive statistics.

- Significance was evaluated by t-test for continuous variables and Chi-square test for discontinuous variables.

- For the values ​​repeatedly measured at time intervals, the difference between the two groups was compared using a mixed effect model.

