| **Study method** | - Patients who are scheduled to undergo gastrectomy for stage 1 gastric cancer are randomly assigned either to the mHealth group or the face-to-face counseling group. Patients in the mHealth group (N=90) will use mobile application for 3 months after discharge and those who in the face-to-face counseling group (N=90) will receive general nutrition counseling at 1 month and 3 months after gastrectomy.  - QOL, body component, and nutritional outcomes will be compared between the two groups.  - When obtaining the consent form, the mHealth group will be provided with a simple noom instruction manual and a noom meal record guide, and will be informed of how to use it.  - In addition, individual coaching will be given through articles and messengers on how to manage post-gastrectomy such as weight, diet, and exercise on the mobile app for 3 months from the discharge date.  - Survey response on quality of life at outpatient visits 1, 3, 6, 12 months after surgery  [figure not shown]  * The allowable date of visit at 1, 3, 6, and 12 months after surgery is 1 month before and after. | | | | |
| **Intervention method** | **- mHealth group:** After being discharged from hospital, patients will receive coaching using a smartphone app for 3 months. When the patient is discharged from the hospital, he downloads the Noom app on his or her mobile phone, registers, and then uses the Noom program. In addition, a personal coach is assigned to provide appropriate coaching to the patient on the app.  **-Face-to-Face group:**　Patients will receive individual nutrition counseling from a clinical nutritionist at the hospital at 1 month and 3 months after surgery. | | | | |
| **Evaluation** | Between the mHealth and face-to-face groups  - Comparison of scores of EORTC QLQ-C30 and STO22 at 1, 3, 6, and 12 months postoperatively.  - Comparison of meal amount at 1, 3, 6, and 12 months postoperatively.  - Comparison of body component (BMI, muscle mass, etc) at 1, 3, 6, and 12 months postoperatively.  - Comparison of nutritional outcomes (hemoglobin, albumin, protein, cholesterol) at 1, 3, 6, and 12 months postoperatively | | | | |

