| **Number of research subjects** | - In the results of the pilot study, the eating restriction score of EORTC QLQ-STO22 that was answered at 1 month postoperatively was 30 points. The drop-out rate of the entire study was 30%. Based on this, the following hypothesis was established.  - Among the EORTC STO22 items that patients in the mHealth group responded to 1 month after surgery, the score for the eating restriction item was expected to be 30±10 (mean±standard deviation). The item score for the control group was expected to be 35 points.  - alpha value: 0.05  - power: 80%  → sample size was calculated as 65 cases in each group.  → Considering 30% of drop-out rate, a total of 180 cases (90 cases in each group) is needed.  - If drop-outs are more than expected, the number of sample size can be adjusted through statistical advice. | | | | |
| **Statistical consideration** | **1. Randomization**  - Randomization generally performs permutated mixed block randomization, and is generated in a 1:1 ratio using 2 and 4 mixed block blocks. Using the nQuery Program, a randomly assigned table is created according to the stratification factor and notified through a web-based clinical research management system.  - Stratification factors: extent of gastrectomy (distal vs. total gastrectomy)  2. **Statistical analyses**  - Patient's clinical characteristics are expressed as mean ± standard deviation or ratio using descriptive statistics.  - Significance was evaluated by t-test for continuous variables and Chi-square test for discontinuous variables.  - For the values ​​repeatedly measured at time intervals, the difference between the two groups was compared using a mixed effect model. | | | | |
| **Specimen** | ☑Not applicable | | | | |
| **Plan for secondary use of collected data** | □ Not applicable  □ Use of personal information including personally identifiable information  ☑ Use of personal information except personally identifiable information  □Use of specimen | | | | |
| **Monitoring plan** | ○ This study is conducted through the use of smartphone apps and questionnaires of the subjects, and safety issues are not applicable.  ○ Adverse reactions are not collected because there are no adverse reactions in the use of smartphone apps or surveys. | | | | |

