**3. Study Design**

(1) Study design: single center, prospective, randomization

(2) Research participation period: One year after gastrectomy for early gastric cancer

(3) Data collection period: IRB approval day – 2021. 12. 31

(4) Overall study period: IRB approval day – 2022. 6. 30.

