**6. Patient Recruitment & Registration**

(1) **Research subject recruitment method and procedure**

- For patients who have been diagnosed with stage 1 gastric cancer and are expected to undergo gastrectomy, the attending physician directly explains and obtains consent to patients who meet the selection criteria and exclusion criteria.

- The consent process for participation in the study is to be made voluntarily after the consent is explained in detail to the subject, and the subject has sufficient time to think and ask questions.

- A copy of the consent form signed by the study coordinator is provided to the subject and the original is kept.

(2) **Number of research subjects**

- In the results of the pilot study, the eating restriction score of EORTC QLQ-STO22 that was answered at 1 month postoperatively was 30 points. The drop-out rate of the entire study was 30%. Based on this, the following hypothesis was established.

- Among the EORTC STO22 items that patients in the mHealth group responded to 1 month after surgery, the score for the eating restriction item was expected to be 30±10 (mean±standard deviation). The item score for the control group was expected to be 35 points.

- alpha value: 0.05

- power: 80%

→ sample size was calculated as 65 cases in each group.

→ Considering 30% of drop-out rate, a total of 180 cases (90 cases in each group) is needed.

- If drop-outs are more than expected, the number of sample size can be adjusted through statistical advice.

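### The protocol prints its block sizes (2 and 4), so in this single-centre, effectively open trial a recruiter who tracks assignments could guess the next arm far better than chance

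*Protocol*

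**What the plan says.** Section 9(1) of the protocol and the synopsis (Statistical consideration, Randomization) state the same scheme: "Randomization generally performs permutated mixed block randomization, and is generated in a 1:1 ratio using 2 and 4 mixed block blocks". It is stratified by extent of gastrectomy, distal or total, and by nothing else. Assignments are "notified through a web-based clinical research management system".

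The setting is given elsewhere in the protocol:

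- Section 3: "Study design: single center, prospective, randomization".
- Section 6(1), on recruitment: "the attending physician directly explains and obtains consent to patients who meet the selection criteria and exclusion criteria".
- Synopsis, Study method: "When obtaining the consent form, the mHealth group will be provided with a simple noom instruction manual". The arm is therefore visible at or close to consent.
- Synopsis, Intervention method, for the comparison arm: "Patients will receive individual nutrition counseling from a clinical nutritionist at the hospital at 1 month and 3 months after surgery". The other arm uses a phone app with a personal coach. No blinding is described, and none seems feasible.

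The protocol does not give the proportion of blocks of each size, the number of physicians who recruit, who sees earlier assignments, or any rule that block sizes are withheld from recruiters.

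**The concern.** Two is the smallest block possible at 1:1. With blocks of 2 and 4, a stratum that is one patient ahead in one arm is usually followed by the other arm, and a stratum that is two ahead is always followed by it. The web system hides the next entry on the list, but not what can be inferred from known past assignments and published block sizes.

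This matters because enrolment involves judgement. Inclusion criterion 4 and exclusion criterion 2 (section 4) turn on ability to use the app, or on a caregiver's capacity to be actively involved. The physician also chooses when to approach a patient. The primary outcome is a patient-reported eating-restriction score, and section 6(2) plans for a difference of 5 points (30 versus 35, SD 10). If enrolment were steered by a guess at the next arm, the arms would differ in traits such as motivation. Neither the planned t-test nor the mixed model (sections 7(5) and 9(2)) would remove that difference.

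**Working it through.** The protocol gives no predictability figure to reproduce, so this is a direct calculation.

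**Inputs.** Blocks of 2 and 4, 1:1, two strata (section 9(1)); 180 patients, 90 per arm (section 6(2)).

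**Assumptions.** The recruiter knows every earlier assignment in the patient's stratum. The recruiter guesses the lagging arm when the stratum is unbalanced and tosses a coin when it is balanced. The block-size mix is not stated, so p, the chance that a block has size 2, is varied from 0 to 1.

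**Block of 2.** The second allocation is always made at imbalance and always guessed correctly: 1 at imbalance, 1 correct.

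**Block of 4.** There are six equally likely orders, or three up to swapping the arms:

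- AABB: 3 allocations at imbalance, 2 guessed correctly
- ABAB: 2 at imbalance, 2 correct
- ABBA: 2 at imbalance, 2 correct

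The averages are (3 + 2 + 2)/3 = 7/3 at imbalance and 2 correct.

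**Mixing the sizes.**

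- Share at imbalance = [p + (1 − p)·7/3] / [2p + 4(1 − p)]
- Accuracy there = [p + 2(1 − p)] / [p + (1 − p)·7/3]
- Overall correct = share × accuracy + (1 − share) × 0.5

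| Mix | Share at imbalance | Accuracy there | Overall correct |
| --- | --- | --- | --- |
| all blocks of 4 (p = 0) | 58.3% | 85.7% | 70.8% |
| equal mix (p = 1/2) | (10/3)/6 = 55.6% | 3/(10/3) = 90.0% | 72.2% |
| two-thirds blocks of 2 | 54.2% | 92.3% | 72.9% |
| all blocks of 2 (p = 1) | 50.0% | 100% | 75.0% |

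A simulation of 180 patients in two strata, equal mix, gave 55.2% at 90%.

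**By size of imbalance, equal mix.** Per six allocations, 3 are made at imbalance 1 (50.0%), with 8/3 guessed correctly: 88.9%. One third is made at imbalance 2 (5.6%), always guessed correctly.

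**Less informed recruiters (simulation).** One recruiter who knows all assignments but ignores the strata can guess at about 67% of allocations with about 74% accuracy. If two or three physicians each know only their own patients, accuracy is about 53 to 54%.

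**Alternatives, full knowledge assumed.**

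- Blocks of 4, 6 and 8, equally mixed. Expected correct guesses in a block of 2m are m + 0.5(4^m/C(2m,m) − 1), giving 2.833, 4.100 and 5.329. Overall: 12.262/18 = 68.1%. By imbalance: 63.8% of allocations at 78.4% accuracy.
- Maximum-tolerated-imbalance (big-stick) list with limit b: 0.5 + 1/(4b) in the long run. For b = 3, 0.5 + 1/12 = 58.3%. The excess over 50% comes from the 1/(2b) = 1/6 of allocations forced at the limit; the rest are fair coin tosses.

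**Possible bias.** Let d be the difference in expected score between patients enrolled when one arm is guessed and those enrolled when the other is. The difference between arms is then (2 × overall correct − 1)·d. The documents give no d.

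| Scheme | Multiplier | d = 1 point | d = 5 points |
| --- | --- | --- | --- |
| blocks of 2 and 4 | 2 × 0.722 − 1 = 0.44 | 0.4 | 2.2 |
| blocks of 4, 6 and 8 | 2 × 0.681 − 1 = 0.36 | 0.4 | 1.8 |
| big-stick, limit 3 | 2 × 0.583 − 1 = 0.17 | 0.2 | 0.8 |

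**The case against.** The strongest objection is that the high accuracy needs a fully informed recruiter. A reader might infer that the attending physicians see every earlier allocation, so that over half of all assignments are known to them at about 90%. The protocol does not say so. It does not give the number of recruiters or say who receives the web notification, and counselling and coaching are delivered by a nutritionist and an app coach rather than by the consenting physician. This stands: the 90% is conditional, and with divided knowledge most of the advantage disappears.

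A reader might also take 2.2 points as the expected bias. It is not. It needs d = 5, which is half the planned SD and as large as the whole target difference, applied at every enrolment. Nothing in the documents suggests steering. Inclusion criterion 4 also requires app ability, or a caregiver who has it, in both arms, which narrows one route for it.

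A third tempting reading is that larger blocks solve the problem, because the share of allocations guessable at about 90% drops from about 55% to about 2%. That comparison uses two thresholds. At a strict 90% cut the change is from 5.6% to about 2%, because imbalance 1 under the present scheme is guessed at 88.9%. Under blocks of 4, 6 and 8 more allocations become guessable, each less accurately.

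Finally, the scheme is stratified, mixes its block sizes and is released by a web system, so this is a design weakness rather than an error or contradiction. That is right. But the block sizes are fixed in the protocol itself, not left to a later document, and nothing says they are withheld from recruiters.

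**Conclusion.** The point holds as a conditional vulnerability. Under full knowledge of past assignments within a stratum, the present scheme lets a recruiter guess about 56% of allocations with about 90% accuracy and 72% correctly overall, if the sizes are equally mixed. The range over every possible mix is 50 to 58% of allocations at 86 to 100% accuracy. Full knowledge is plausible with one centre, two strata and visible arms, but it is an assumption, and with knowledge split between two or three recruiters accuracy is close to chance.

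Any resulting bias is about 0.44 times a steered score difference that the documents do not supply. For 1 to 5 points, that is 0.4 to 2.2 points against a planned difference of 5. The calculation shows exposure to selection at enrolment; it does not show that selection occurred. The change is worth making because it is cheap and the planned analyses could not undo the bias if it arose.

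**What to change.** In section 9(1) and the matching synopsis entry:

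1. Remove the block sizes. State that the details of the scheme are kept only in a statistician-held randomisation specification and withheld from everyone who recruits.
2. Drop block size 2.
3. Preferably generate the distal and total gastrectomy lists with a maximum-tolerated-imbalance (big-stick) procedure, limit 3, and withhold the limit too, since allocations at the limit are forced. Larger mixed blocks such as 4, 6 and 8 are an acceptable second choice, but alone they lower overall correct guessing only from 72% to 68%.

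The cost is one sentence of protocol text, a new list, and a possible end-of-trial imbalance of up to 3 patients per stratum with the big-stick limit (up to 4 with blocks of 8). If both strata ended 3 apart in the same direction, the arms would be 93 and 87. The variance of the difference would rise by the factor 180²/(4 × 93 × 87) = 1.001, about 0.1%, which is negligible at 90 per arm.

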**10. Interim analysis**

Not applicable

**11. Safety**

(1) This study is conducted through the use of smartphone apps and questionnaires of the subjects, and safety issues are not applicable.

(2) Adverse reactions are not collected because there are no adverse reactions in the use of smartphone apps or surveys.

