**1. Background**

**(1) Changes in the diet of patients after gastrectomy**

- Patients who underwent gastrectomy experience the following anatomical changes.

[figure not shown]
- Patients suffer from gastrectomy syndrome due to resection of the pylorus, which regulates the speed of food movement between the stomach and small intestine. Gastric resection syndrome includes abdominal pain, diarrhea, nausea/vomiting, increased pulse, weakness, and hypoglycemia that occur after eating.

- In particular, when the patient rushes to eat or eats a large amount of food, and eats high-sugar foods, gastrectomy syndrome can be severely experienced.

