**(2) Dietary adaptation of the patient**

- Patients receive nutritional counseling during the hospitalization period, but when they return to their daily life after discharge, there is no separate education on how to eat and how to adjust, resulting in various trials and errors.

- In particular, after being diagnosed as a cancer patient, there are cases where people around us hear unverified stories and eat mainly with certain foods, or they may not be able to consume enough nutrition due to restrictions on certain foods.

- They are also not well aware of postgastrectomy syndrome, so they constantly experience discomfort after eating.

- This postgastrectomy syndrome is most severe in the early postoperative period and gradually relieves after dietary adaptation.

(3) **Diet management using a smartphone app**

[figure not shown]
- Currently, for weight loss, a smartphone app (Noom) is being used that keeps a daily meal diary, calculates meal calories, and provides 1:1 customized coaching service.

- Noom not only makes it easy for users to enter the food eaten during the day based on the food database, but also helps the coach in charge check daily to keep the dietary control.

- If Noom is used in the process of dietary adaptation after surgery for gastric cancer patients, it is expected that balanced nutritional intake will be achieved through appropriate dietary disorders. In addition, by providing information on gastrectomy syndrome, it is possible to reduce and prevent gastrectomy syndrome.

- Also, as Noom actively encourages exercise therapy, the patient is motivated for proper exercise.

- This is expected to reduce the patient's symptoms and improve the quality of life.

(4) **Previous literature review**

- In the past literature, the results that weight control and metabolic syndrome control were significantly improved when using a smartphone app were published in several papers.

- There have also been studies showing that breast cancer survivors, which are highly related to obesity, lose weight, increase vegetable intake, and increase exercise volume when nutritional control using a smartphone app is used.

- Regarding stomach cancer, a study on improving lung capacity with a mobile self-monitoring tool has been published, and studies related to nutrition or diet have only been introduced with protocols so far.

[figure not shown]

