**(4) Drop-out criteria**

1. Patients who have not undergone distal gastrectomy or total gastrectomy

1. The pathology test result is stage II or higher after gastrectomy
2. Patients who need adjuvant chemotherapy after gastrectomy

4. The hospital stay exceeds 3 weeks due to complications

5. Patients request withdrawal of participation

6. Patients having difficulty in collecting data suitable for the purpose of the study because they have not visited at all 1, 3, 6, and 12 months

1. **Study diagram**

|  | Informed consent | |  |
| --- | --- | --- | --- |
|  |  |  |  |
|  | Screening | |  |
|  |  |  |  |
|  | Gastrectomy | |  |
|  |  |  |  |
|  | Follow-up at 1, 3, 6, 12 months after operation | |  |

| **Data** | **Preop** | **Op** | **POD5** | **POD1m** | **POD3m** | **POD6m** | **POD12m** |
| --- | --- | --- | --- | --- | --- | --- | --- |
| age, sex, height, past medical history, smoking, alcohol, concomitant medications | O |  |  |  |  |  |  |
| operating day, operation method |  | O |  |  |  |  |  |
| pathological results of gastric cancer, postoperative complications |  |  |  | O |  |  |  |
| body weight | O |  | O | O | O | O | O |
| body component such as muscle mass measured with a body composition analyzer | O |  |  | O | O | O | O |
| EORTC QLQ C30, STO22 | O* |  |  | O | O | O | O |
| Hb, Protein, Albumin, Cholesterol | O |  | O |  | O | O | O |

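### Adverse-event collection is ruled out on a premise about apps and surveys that does not fit diet coaching after gastrectomy, so discrete harms go unrecorded in both arms

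*Protocol*

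**What the plan says.** Section 11 (Safety) has two statements. The first is "This study is conducted through the use of smartphone apps and questionnaires of the subjects, and safety issues are not applicable". The second is "Adverse reactions are not collected because there are no adverse reactions in the use of smartphone apps or surveys". The synopsis repeats both under its monitoring plan, so this is a decision fixed in the protocol and not a detail left open.

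The programmes being compared are described elsewhere:

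- **mHealth arm** (synopsis, study method): "individual coaching will be given through articles and messengers on how to manage post-gastrectomy such as weight, diet, and exercise", for three months from discharge. Section 1(3) gives the app's present use: "Currently, for weight loss, a smartphone app (Noom) is being used that keeps a daily meal diary, calculates meal calories".
- **Face-to-face arm** (synopsis, intervention method): "Patients will receive individual nutrition counseling from a clinical nutritionist at the hospital at 1 month and 3 months after surgery".
- **Symptoms** (section 1(1)): the syndrome after gastric resection includes vomiting, "weakness, and hypoglycemia that occur after eating". The same section says that hurried eating, large amounts and sugary food can make it severe.

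**The concern.** The reason given for collecting nothing concerns the delivery channel (an app) and the measuring tool (a questionnaire). What is randomised is advice on eating, weight and exercise in patients recovering from gastrectomy. The protocol expects this advice to lessen the syndrome. Advice that can lessen such events cannot be assumed incapable of worsening them, and the comparator is dietary advice as well.

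What is at stake is the balance of the conclusion. If the app arm does better on the eating-restriction score, the report would have no comparative record of acute events to set beside that result. The primary endpoint and its analysis are not affected.

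**Working it through.** **1. What could reveal harm, and what could not**

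| Item | Planned? | Where |
| --- | --- | --- |
| Body weight | Before surgery, day 5, then 1, 3, 6, 12 months | Study diagram table; secondary endpoint in 2(2) |
| Body composition | Before surgery, then 1, 3, 6, 12 months | Study diagram table; 2(2) |
| Hemoglobin, protein, albumin and cholesterol | Before surgery, day 5, then 3, 6, 12 months | Study diagram table; 2(2) |
| QLQ-C30 and STO22 | Before surgery, then 1, 3, 6, 12 months | Study diagram table; 7(2) |
| Complications | Recorded, timing unclear (step 2); no comparison between arms listed | Study diagram table; 8(2) |
| Readmission, emergency visit | No item | 7(1), 12(2) |
| Hypoglycemic episode | No item; glucose is not among the laboratory tests | 7(1) |

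The first four rows are compared between arms (sections 7(2) and 7(5)). The last three are not.

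**2. Timing of complications**

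In the study diagram table, the row "pathological results of gastric cancer, postoperative complications" has one mark, at 1 month. In the schedule of section 8(2), the row that includes complications is marked at screening and under one undivided follow-up column. The study diagram defines follow-up as 1, 3, 6 and 12 months. The first table points to one recording and the second can be read as four. The protocol does not settle which applies. Visits may also fall one month either side of the nominal date (section 8(1)), so the 1-month entry could be made as late as month 2.

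**3. Scale**

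The protocol gives no event rate, so the rates below are assumptions.

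*The plan's own figure.* Section 6(2) assumes means of 30 and 35, SD 10, alpha 0.05 (taken as two-sided) and 80% power:
n = 2 × (1.96 + 0.84)² × 10² / 5² = 2 × 7.85 × 4 = 62.8, so 63 per arm (64 by the exact t-test). The stated 65 is close. It also states 90 randomised per arm.

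*Group-level worsening.* The detectable difference in a continuous outcome at 80% power is (1.96 + 0.84) × √(2/n):
- n = 65: 2.80 × 0.175 = 0.49 SD
- n = 90: 2.80 × 0.149 = 0.42 SD

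*Upper limit if events were recorded and none occurred.* One-sided 95% limit = 1 − 0.05^(1/n):
- n = 65: 4.5%
- n = 90: 3.3%

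*Chance of at least one event in an arm*, 1 − (1 − p)^n:

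| Assumed true rate | n = 65 | n = 90 |
| --- | --- | --- |
| 1% | 48% | 60% |
| 2% | 73% | 84% |
| 5% | 96% | 99% |

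*Comparing rates.* For an assumed 5% against 15% with 90 per arm, using the pooled SE for the test (0.0447) and the unpooled SE for power (0.0441): (0.10 − 1.96 × 0.0447) / 0.0441 = 0.28, which gives 61% power. With 63 per arm (90 × 0.7) it is 46%. The trial is large enough to describe such events but not to test them.

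**The case against.** The strongest reply is that the plan is not blind to harm. Weight, body composition, nutritional laboratory values and EORTC scores are measured in both arms to 12 months and compared, and a shift of about half a standard deviation would be seen. That stands. A reader might infer from section 11 that the trial cannot detect harm at all, or that excess weight loss would be missed. The documents do not support either reading, since body weight is a named secondary endpoint.

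Three other stronger readings also fail:

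- *Nothing is recorded after 1 month, so most of the app period is uncovered.* This relies on the study diagram table alone. Section 8(2) marks complications under follow-up, so the uncovered share cannot be worked out.
- *A weight-loss product is being used on patients who should not lose weight.* Weight loss is the app's existing public use. Here the coaching concerns management after gastrectomy, and nothing suggests that it promotes the eating habits the protocol warns against.
- *Patients lost through harm would vanish as plain drop-outs.* The drop-out criteria are listed by reason, and the pilot reported its drop-outs by reason. What is missing is only a requirement to report them by arm and to note whether an adverse event lay behind a withdrawal.

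It is also fair to say that the added items lie outside the personal information listed in section 12(2), so that list would need amending.

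None of this repairs the premise of section 11 or provides a record of discrete events.

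**Conclusion.** The point holds in a limited form. The ground for not collecting adverse events does not match the intervention and sits badly with the protocol's own account of how eating affects symptoms. Readmissions, emergency visits and hypoglycemic episodes are neither recorded nor compared in either arm. The recording of complications after 1 month is contradictory between two tables.

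As to size, recording would allow a zero count to exclude, with one-sided 95% confidence, a rate above about 4.5% (65 per arm) or 3.3% (90 per arm). Without recording, no limit can be given. These limits assume complete ascertainment in the stated number of patients; they illustrate what is forgone and do not suggest that such events are expected. This is an improvement that should be made, not a flaw that invalidates the primary comparison.

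**What to change.** 1. In section 11 and the synopsis monitoring plan, delete the premise that no adverse reactions exist and the statement that none are collected.
2. Reconcile the study diagram table with the schedule in section 8(2), so that both show complications recorded at the 1-, 3-, 6- and 12-month visits.
3. At those visits, also record readmissions, emergency visits and hypoglycemic episodes, from the medical record and patient report. Use the same questions and sources in both arms. App users have a coach who checks daily, so events known only through coaching messages would be found more readily in one arm.
4. Tabulate these events and the reasons for drop-out by randomised arm, including patients dropped for complications. Keep this descriptive, given the power shown above. Coaching starts at discharge, so identify complications before discharge separately.

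**Cost:** one extra case-report page at visits that already take place, and a small addition to the list of collected data in section 12(2) and its synopsis counterpart. Searching the medical record is already a stated purpose there. No new visit or procedure is needed.

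### Section 11 waives adverse-event collection for a reason that fits the app as a medium but not the coaching it delivers, so discrete events over the coaching period are not listed for collection or comparison by arm

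*Protocol*

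**What the plan says.** Section 11 makes two statements, and the synopsis repeats both under its monitoring plan. The first sets the scope: "This study is conducted through the use of smartphone apps and questionnaires of the subjects, and safety issues are not applicable". The second is the rule and its reason: "Adverse reactions are not collected because there are no adverse reactions in the use of smartphone apps or surveys".

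Elsewhere the protocol describes what the mHealth arm receives and in whom:

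- Synopsis, study method: "individual coaching will be given through articles and messengers on how to manage post-gastrectomy such as weight, diet, and exercise on the mobile app". This runs for three months from the discharge date.
- Section 1(3), on the product's present use among the general public: "Currently, for weight loss, a smartphone app (Noom) is being used that keeps a daily meal diary, calculates meal calories". The same section says a coach checks daily, and adds: "Also, as Noom actively encourages exercise therapy, the patient is motivated for proper exercise".
- Section 1(1), on the patients: "Gastric resection syndrome includes abdominal pain, diarrhea, nausea/vomiting, increased pulse, weakness, and hypoglycemia that occur after eating". It adds that rushing, large amounts and high-sugar food make this worse. Section 1(2) says the syndrome is worst early after surgery.

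**The concern.** The waiver is a positive instruction not to collect, so a statistical analysis plan cannot repair it: events that nobody records cannot be analysed. The instruction rests on a description of the exposure that the rest of the protocol does not share. An app or a questionnaire as such may well be harmless. Coaching that is meant to change how recently operated patients eat and exercise is a different exposure. The protocol expects it to reduce post-gastrectomy symptoms, and an intervention expected to move those symptoms cannot be declared in advance unable to move them the wrong way.

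At stake is the safety information from the trial. If a few patients in one arm had an unplanned admission or symptomatic hypoglycaemia, the planned outcomes, which are compared as group means, might not show it.

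**Working it through.** Section 11 gives no figure, so the main check sets the protocol's sections side by side. Arithmetic is used only for what a by-arm event comparison could show.

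**1. Reason against exposure.** The reason in Section 11 names apps and surveys. The synopsis and Section 1(3) name coaching on weight, diet and exercise. Section 1(1) ties vomiting, weakness and hypoglycaemia to eating. The reason does not address the coaching content.

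**2. What is recorded, and what is compared by arm.**

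| Item | Recorded (data table, study diagram) | By-arm comparison (Sections 2(2), 7(2), 7(5)) |
|---|---|---|
| Body weight | Pre-op, day 5, 1, 3, 6, 12 months | Yes, with BMI |
| Body composition | Pre-op, 1, 3, 6, 12 months | Yes |
| Haemoglobin, protein, albumin, cholesterol | Pre-op, day 5, 3, 6, 12 months | Yes (Section 7(2) also lists 1 month, where the table has no draw) |
| EORTC QLQ-C30, STO22 | Pre-op, 1, 3, 6, 12 months | Yes |
| Postoperative complications | 1 month | None listed |
| Unplanned admission, emergency visit, symptomatic hypoglycaemia as events | Not listed | None listed |

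The comparisons listed are of scores or means (t-test, mixed model).

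**3. Coverage of the coaching period.** Coaching ends three months after discharge, hence at least 3 months after surgery. Complications are recorded at 1 month, with a visit window of 1 month either side, so at 2 months at the latest. At least 3 − 2 = 1 month of coaching is uncovered, and at least 3 − 1 = 2 months at the nominal date. The coarser schedule in Section 8(2) marks complications under a single follow-up column. It does not say which visits, so it does not settle the matter.

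**4. What a by-arm event comparison could show.**

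- Plan's own size: difference 35 − 30 = 5, SD 10, alpha 0.05 (two-sided assumed), power 80%. n = 2 × (1.96 + 0.8416)² × 10² / 5² = 2 × 7.849 × 4 = 62.8, so 63 per arm; 64 with the t distribution. The stated 65 is within two patients.
- Evaluable per arm after the planned 30% drop-out: 90 × 0.70 = 63.
- For two proportions, n per arm = [1.96√(2p̄(1−p̄)) + 0.8416√(p₁(1−p₁) + p₂(1−p₂))]² / (p₂−p₁)². With p₁ = 0.10 and p₂ = 0.298: (1.107 + 0.460)² / 0.198² = 2.456 / 0.0392 = 62.6, so 63.
- The 95% CI half-width for a risk difference, if both arms have rate p, is 1.96√(2p(1−p)/63).

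The documents give no event rates, so the control rates are assumed and shown as a range:

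| Assumed control rate | App-arm rate detectable, 80% power, 63 per arm | Same, all 90 per arm | CI half-width, 63 per arm |
|---|---|---|---|
| 5% | 21.9% | 18.4% | 7.6 points |
| 10% | 29.8% | 26.0% | 10.5 points |
| 20% | 43.0% | 39.0% | 14.0 points |

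Only large differences would be detected. Event reporting would describe what happened and would not test a safety hypothesis.

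**The case against.** Much of the case on the other side stands.

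- **Harm-relevant outcomes are compared.** A reader might infer that harm is never compared by arm, or that the chance of recording it is nil. The documents do not support that. Weight, BMI, muscle mass, blood values and EORTC scores are compared by arm through 12 months, Section 7(5) states no direction for its tests, and complications are recorded once. Excess weight loss in the app arm would appear as a difference in its disfavour. The gap is confined to discrete events.
- **No safety claim is planned.** A reader might infer that the trial intends to conclude that the app is harmless. No objective or endpoint says so; Section 11 only declares safety not applicable. What remains is that the absence of adverse reactions is asserted before any data.
- **The product is adapted to these patients.** Section 1(3) gives weight loss as its general use, then describes the trial use as balanced intake and information about the syndrome. The documents do not show that the coaching causes harm, nor does this point claim it. Nor does the point need the app to displace nutritionist sessions: Section 12 lists nutrition education as participant support without naming an arm.
- **The pilot named no harm among its drop-outs** (four for stage, two refusals). But its listed outcomes include no adverse events, so this says little.
- **These symptoms are expected in both arms.** They follow from the gastrectomy. One might size the gap by the chance of seeing at least one case in the app arm, but such a case would say nothing about coaching. The relevant quantity is the between-arm difference, for which the trial has little power.

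None of this repairs the stated reason or records the missing events.

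**Conclusion.** The concern holds in a limited form. Adverse-event collection is waived for a reason that describes the medium and not the coaching, and the protocol's own account of the coaching and the patients contradicts it. As a result, events such as unplanned admissions, emergency visits and symptomatic hypoglycaemia are not listed for collection through the coaching period, and neither complications nor events are listed for comparison by arm. The trial can support no safety statement beyond its body-composition, laboratory and questionnaire outcomes.

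The consequence is moderate. The primary estimate, its test and the sample size do not change. The number of events missed cannot be estimated from the documents, and a by-arm comparison would be imprecise. The conclusion rests on the visit-level data table being the full list of what is recorded. The power figures rest on assumed control rates of 5% to 20%. The change is still worth making, because events not asked about at the time are hard to recover reliably later.

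**What to change.** 1. Delete the statements that safety issues are not applicable and that there are no adverse reactions, in Section 11 and in the synopsis monitoring plan. Reconcile these sections with the description of the coaching (synopsis study method, Section 1(3)), the account of post-gastrectomy symptoms (Section 1(1)), and the complications entries in the study-diagram data table and the Section 8(2) schedule.
2. At the existing 1, 3, 6 and 12 month visits, ask both arms, in identical wording, about unplanned admissions or emergency visits and about symptomatic hypoglycaemia or vomiting since the last visit.
3. Report by randomised arm, descriptively: these events and the recorded complications as counts with a risk difference and 95% CI, and percentage weight loss from the pre-operative weight, which needs no new data.
4. State that about 63 evaluable patients per arm give low power for event differences, so that absence of a significant difference is not read as evidence of safety.

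The cost is a short amendment, one CRF page and a little more data entry. No new visit, test or staff is needed.
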